## 1.2 Virosomes

There is mounting evidence that the majority of natural anti-malarial immune responses (and accordingly responses to entire recombinant malaria proteins) are useless or even counterproductive. Therefore our approach is, to focus the immune response to selected protective epitopes of key malaria antigens.

We have developed new approaches and technologies for the design of epitope-focussed vaccines [1-6]. Starting point was to investigate the possibility of associating peptide or protein antigens in a defined fashion using immunopotentiating reconstituted influenza virosomes (IRIV). These are spherical, unilamellar vesicles, prepared by detergent removal from a mixture of natural and synthetic phospholipids and influenza surface glycoproteins. They have been shown to be a highly effective means of enhancing the immune response to a variety of antigens. The haemagglutinin membrane glycoprotein of the influenza virus plays a key role in the activity of IRIV. This major antigen of influenza virus is a fusion-inducing component, which facilitates antigen delivery to immunocompetent cells. In the hepatitis A vaccine Epaxal, the first licensed vaccine in which IRIV are used as a delivery system for a non-influenza antigen, the hepatitis A antigen spontaneously binds to the IRIV. We have developed and evaluated a method to couple antigens to phosphatidylethanolamine and to integrate the phospholipid-antigen conjugates into the virosome membrane during the virosome reconstitution process. In experiments in mice, the presentation of multiple copies of the antigen on the virosome surface induced strong antibody responses.

## 1.3 Malaria antigens

The next step was to couple mimotopes of surface loops of malaria antigens to the surface of the virosomes. Due to their inherent flexibility, linear peptides often elicit antibodies that bind to denatured proteins, but fail to recognize the same sequences in native protein structures. This is one problem that has so far hindered the application of synthetic peptides in vaccine design. Other problems are that peptides in serum have only a limited stability against proteolysis, and that their immunogenicity when administered as conjugates in human-compatible adjuvants is often weak. We have now shown that these problems may be alleviated by using conformationally defined peptidomimetics coupled to virosomes. We have

identified and optimized conformationally restricted cyclic peptide structures that mimic surface loops of two key malaria vaccine candidate antigens; the NPNA repeat region of circumsporozoite protein (CSP) and the apical membrane antigen-1 (AMA-1).

Starting with a small cyclic peptide containing portions of the NPNA-repeat region of CSP we have identified and profiled an optimized mimotope, which very efficiently elicits antibodies which cross-react with *P. falciparum* sporozoites and inhibit sporozoite invasion of human liver cells. These results demonstrated that it is possible to start from a lead structure and design a compound with optimal immunological properties in a stepwise process. With AMA-1, we used two alternative approaches to identify a lead structure for mimotope development. The first approach, immunological studies with a library of synthetic template-bound cyclic 12-mer peptidomimetics, turned out to be less successful than a second strategy in which a larger synthetic peptide structure was used as a starting point. Some of the monoclonal antibodies (mAbs) generated against this structure had growth-inhibitory activity against blood stage parasites *in vitro*.

We compared a mimotope-virosome formulation with the same mimotope presented as a multiple antigenic peptide (MAP) construct, in which several copies of the mimotope are adsorbed to an alum-adjuvant. Both formulations elicited comparable levels of anti-mimotope antibody responses in mice. However, only the antibodies against the virosome formulation bound to the parasites. This indicated that phosphatidylethanolamine-coupled antigens were located on the surface of the virosomes without their conformation being disturbed, whereas adsorption to alum dramatically disturbed their conformation.

Our joint preclinical research has identified the two virosome products PEV 301 (incorporating an Apical Membrane Antigen-1 mimotope) and PEV 302 (incorporating a Circumsporozoite Protein mimotope), which we regard as suitable components of a virosome malaria vaccine.

## 1.4 Rationale

No vaccine exists today against malaria. Attempts to produce a multi-stage subunit vaccine against the malaria parasite *Plasmodium falciparum* have so far met with limited success. Cumulated experience with the clinical profiling of previous malaria vaccine candidates indicates that new strategies both for the targeting of the immune response to suitable antigenic determinants of the parasite and for the safe and appropriate delivery of antigens are required. We therefore have developed an alternative approach for the design of a malaria vaccine, which is based on the delivery of peptidomimetics by immunostimulating influenza virosomes (IRIV's).

IRIV represent an adjuvant carrier system that is already incorporated in two vaccines registered for human use (EU and Canada). More than 5 million IRIV-based vaccine units have been applied so far, proving that the virosomes induce a fast and very specific immune response and are very well tolerated. Our preclinical research has demonstrated that it is possible to induce malaria parasite growth and invasion inhibitory antibodies by delivering synthetic peptidomimetics of crucial protein surface loops of different parasite development stages on the surface of IRIV to the immune system.

Sequential rounds of peptidomimetic optimization have lead to the definition of two candidate components (PEV 301 and PEV 302) for a virosomal multi-stage malaria vaccine. In experimental animals, these induce highly effective antibody responses against the merozoite and the sporozoite stages of the parasite, respectively. After an appropriate preclinical profiling, toxicological studies and GMP manufacturing, these two components are now ready for clinical testing.

Based on previous experience with the two registered IRIV-based vaccines and the highly defined nature of the two synthetic malaria peptidomimetics we expect that the candidate vaccine components will exhibit an excellent safety profile. Our approach to use conformationally defined, synthetic peptide mimetics combined with the validated virosome technology for antigen delivery should overcome many drawbacks associated with other approaches for the design of a malaria subunit vaccine.

## 1.5 Benefits and Risks

Volunteers will not benefit directly from participation in this study. However, it is hoped that the information gained from this study will contribute to the development of a safe and effective malaria vaccine. The general risks to participants in this Phase I study are associated with phlebotomy and with vaccination. The volume of blood drawn over the study should not compromise these otherwise healthy subjects. Potential risks include the following:

**Local reactions:** Mild tenderness, bruising, or fainting may result from venipuncture. An inflammatory reaction as manifested by redness, swelling, and/or tenderness may occur at the site of vaccine injection. All these local reactions have spontaneously resolved within weeks.

**Systemic Reactions:** Systemic reactions to immunization could theoretically occur, and include a flu-like illness with low-grade fever, chills and malaise. However, experience to date with other CSP vaccines suggests that if such reactions occur, they resolve in 12 days without therapy or limitation of daily activity. Serum sickness reactions due to deposition of antigen-antibody complexes, or idiosyncratic immune responses not dependent on immune complexes could theoretically develop resulting in damage to organs, such as the liver or kidney. Such immunemediated reactions have not been reported to date after malaria vaccines. Temporary ascending paralysis, the Guillain-Barré syndrome, may occur with any vaccine, although it is very rare.

**Allergic Reactions and Anaphylaxis:** As with any vaccine, allergic reactions are possible. A variety of synthetic and recombinant malaria peptide vaccines have induced systemic allergic responses, e.g., urticaria and anaphylaxis. The allergic reactions occurred after 2-3 vaccinations administered at intervals of 1 month or more, vaccines were formulated with Alhydrogel or QS-21 adjuvants, and high antigen concentrations (200 µg - 2000 µg) were inoculated with each dose. Reactions were occasionally associated with development of antigen-specific IgE antibody.

**Adventitious Agents:** Each lot of vaccine is tested for sterility and for either endotoxin content or pyrogenicity. The formulated product is released for use in humans when the release criteria are met, which suggests that the product is free of known microbial contamination that could infect humans. Nevertheless, the risk of unknown microbe is always present.

## 2 Objectives

### 2.1 Primary objective

To demonstrate the safety and tolerability of two virosome formulated malaria peptidomimetics given alone and in combination.

### 2.2 Secondary objective

To determine the immune response (humoral and cell mediated) against two virosome formulated malaria peptidomimetics given alone and in combination.

## 3 Study Design

This prospective phase I, single centre, randomized, single blind, placebo controlled, dose escalating study will be conducted in 46 healthy adult volunteers. Eligible study participants will be randomized into six groups: PEV 301 10 µg (group A, n = 8) or PEV 302 10 µg (group B, n = 8) or PEV 301 50 µg (group C, n = 8) or PEV 302 50 µg (group D n = 8) or PEV 301 50 µg plus PEV 302 50 µg (group E, n = 8) or virosomes alone (group F, n = 6).

Study participants will be vaccinated three times, i.e. at days 1, 64(+2) and 183(+2) and followed-up 3 times after each vaccination. If any of the study groups does not show any immune response 3 weeks after the 2nd vaccination, no 3rd vaccination will be given to that group, i.e. the study for that group will be terminated 3 weeks after the 2nd vaccination.

Groups C & D (PEV 301 50 µg; PEV 302 50 µg) will be started 5 weeks after the 1st vaccination of groups A, B.

Group E (PEV 301 plus PEV 302) will be started 5 weeks after the 2nd vaccination of groups C and D.

Group F will be distributed and serve as a control in all groups receiving the active product.

The total duration of the study for each participant is 31 weeks, the number of visits is 13.

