| IMMUNOGENICITY                 | TIMING OF SPECIMEN SAMPLING for HUMORAL RESPONSE  | At baseline (during screening), at the day of the 2 nd and 3 rd vaccination (samples to be taken prior to vaccination), and 21 (+5) days after each vaccination.                                                                                                                                                                                                                                                                                                                                                                                                                                                                                                                                                                                                                                                                                                                                                                                                                                                                                                                                                                                                                                                                                                                                                                                                                                                                                                                                                                                                                                                                                                                                                    |

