| INTERIM REPORT                             | 
An interim analysis will be performed after obtaining the results following the second injection of vaccine. Data will be collected in study weeks 12-14 (visit 9). If no humoral or cell mediated immune response is seen or the response considered sufficient in one of the study groups after 2 vaccinations, the study for this group will be terminated, i.e. no 3rd vaccination will be given.
                                                                                                                                                                                                                                                                                                                                                                                                                                                                                                                                                                                                                                                                                                                                                                                                                                                                                                                                                                                                                                                                                                                                                                                                                                                                                                                                                                                                                                                                                                                                                                                                                                                                                                                                                                                                                                                                                                                                                                                                                                                                                                                                                                                                                                                                                                                                                                                                                                                                                                                                                                                                                                                                                |                     |                                                                                                                                                          |                 |                                          |

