## 8.2 Surveillance period for occurrence of adverse events

All adverse events occurring within one month (minimum 30 days) following administration of each dose of vaccine/ placebo must be recorded on the Adverse Event Form in the subject's CRF, irrespective of severity or whether or not they are considered vaccination-related.

Additionally, all serious adverse events brought to the attention of the investigator during the period starting from the day of performance of the first study procedure for each subject and ending not earlier than six months (minimum 180 days) following administration of the last dose of study vaccine for that subject must be recorded. See 8.8 for instructions for recording and reporting of serious adverse events.

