## **10.8 Interim analysis**

An interim analysis will be performed after obtaining the results following the second injection of vaccine. Data will be collected in study week 13 (visit 9). If no immune response or a response considered being sufficient are seen in one of the study groups after 2 vaccinations, the study for this group will be terminated, i.e. no 3rd vaccination will be given.

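### Stopping a group after two doses is written as ending its study, so the already scheduled day-183 antibody sample and safety assessment are lost

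*Protocol*

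**What the plan says.** Section 3 (Study Design) deals with a group showing no immune response 3 weeks after dose 2. It gets no third vaccination, and "the study for that group will be terminated 3 weeks after the" second vaccination.

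Section 10.8 widens the trigger: "If no immune response or a response considered being sufficient are seen in one of the study groups after 2 vaccinations", then "the study for this group will be terminated", which it glosses as no third vaccination. The synopsis has the same rule ("the response considered sufficient in one of the study groups after 2 vaccinations, the study for this group will be terminated"). Neither gives an end date.

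Other sections keep dosing and follow-up apart:
- Section 5.2.2 only withholds the third dose from non-responders and ends nothing.
- Section 4.4 lets an individual who must stop vaccine continue other study procedures at the investigator's discretion.
- Section 12.12 has even volunteers who violated entry criteria followed to the end of the study.

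On surveillance, section 8.2 requires "All adverse events occurring within one month (minimum 30 days) following administration of each dose of vaccine/ placebo must be recorded". It also requires serious adverse events to be recorded over a period "ending not earlier than six months (minimum 180 days) following administration of the last dose of study vaccine" for that subject. Section 8.6 follows non-serious events until the end of the study.

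On sampling, the synopsis places a humoral sample on the days of the second and third vaccinations ("samples to be taken prior to vaccination"). The Schedule of Assessments gives the same visit, days 176-187, a safety blood sample and an adverse event assessment before the injection.

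**The concern.** The sample on the day of the third vaccination is drawn before the injection, so it does not depend on the injection being given. Once stopping the vaccine is equated with ending the group's study, nothing in the protocol secures that sample. The loss falls on a whole group and is decided by that group's immune result.

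It matters most for a group stopped because its response was judged sufficient. The reason to forgo a third dose is then that two doses are enough, and the one later sample that could show whether the response holds is not taken. Section 10.6 c compares groups at each time point, so the day-183 comparisons also fail whenever either group was stopped.

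A second, weaker issue is that ending a group's study 3 weeks after dose 2 is hard to square with the section 8.2 windows, which run longer from that same dose.

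**Working it through.** **Inputs.** Vaccination on days 1, 64 (57-66) and 183 (176-187): section 5.2.2. Last visit 21 to 26 days after each dose: Schedule of Assessments, footnote d. Windows of at least 30 days after each dose and 180 days after the last dose: section 8.2. Interim timing: Flow Chart. Study length of 31 weeks: section 3.

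**The plan's own figure.** From screening on day -7 to the last visit:
- nominal: 183 + 21 = day 204, and (204 + 7)/7 = 30.1 weeks
- latest: 187 + 26 = day 213, and (213 + 7)/7 = 31.4 weeks

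This agrees with 31 weeks, so the day count is being read as intended.

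**What a stopped group loses.** The section 3 end date is 64 + 21 = day 85.
- The pre-dose-3 sample is due 183 - 85 = 98 days after that date.
- It falls 183 - 64 = 119 days after dose 2; the visit windows allow 176 - 66 = 110 to 187 - 57 = 130 days.
- Humoral samples are scheduled at screening and on days 22-27, 57-66, 78-96, 176-187 and 197-213. After the 3-week sample that follows dose 2, only the one on days 176-187 still reflects two doses alone.
- That visit also has 5.5 + 2.7 = 8.2 mL of safety blood and the adverse event assessment.

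**Comparisons lost at day 183.** Section 10.6 c implies four: A with C, B with D, E with C, and E with D. Stopping A or B removes one. Stopping C, D or E removes two. If the sample were kept, all four would remain like for like, because every group has had two doses at that point.

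**Fit with section 8.2 for a stopped group.**
- 30-day window: ends on day 64 + 30 = 94, which is 94 - 85 = 9 days after the stop (9/30 = 30%), or 30 - 26 = 4 days if the visit is at +26.
- 180-day window: ends on day 64 + 180 = 244, which is 244 - 85 = 159 days after the stop (159/180 = 88%), or 180 - 26 = 154 days if the visit is at +26.

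**The same count for volunteers who receive all three doses.** Last visit on day 204; windows end on 183 + 30 = 213 and 183 + 180 = 363. The gaps are 213 - 204 = 9 days and 363 - 204 = 159 days, identical to those above.

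**When the decision is made** (Flow Chart, study weeks):

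| Groups | Dose 2 | Interim | Interval | Dose 3 |
|---|---|---|---|---|
| A, B | 10 | 16 | 6 weeks (42 days) | 27 |
| C, D | 15 | 22 | 7 weeks (49 days) | 32 |
| E | 29 | 36 | 7 weeks (49 days) | 46 |

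The decision therefore comes 42 to 49 days after dose 2. The 30-day window has already closed, and the 3-week end date lies 42 - 21 = 21 to 49 - 21 = 28 days in the past. The day-183 visit is still 10 to 11 weeks ahead, so it can be kept.

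**The case against.** The strongest reply concerns safety. A reader might infer that stopping a group cuts off 30% of its adverse event window and 88% of its serious adverse event window, so that primary safety data go missing for whole groups. The documents do not support that:
- Fully vaccinated volunteers have exactly the same gaps after dose 3. They come from the general visit schedule, not from stopping.
- The serious-event duty in section 8.2 runs from the subject's own last dose and covers events brought to the investigator's attention. Section 8 tells volunteers to report over the same period. Neither requires a visit, and both can be read as surviving the stop.
- The 30-day window has closed before the interim decision, so that conflict is mainly one of wording.
- Section 10.7.1 evaluates safety at the scheduled assessments, and by the interim a stopped group has had all those tied to dose 2.

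On immunogenicity, the dated end in section 3 applies only to a group with no response, where there is no two-dose response whose persistence could be measured. For a sufficient response no date is given, and section 10.8 explains termination as giving no third vaccination, which might mean only that dosing ends. Immunogenicity is a secondary objective, and section 10.5 says the study is not powered for differences between regimens.

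The safety reply stands, and it reduces that half of the point to a need for clear wording. The reply on the sample stands only in part. The milder reading of section 10.8 is possible, but nothing states that a stopped group returns on day 183, and section 3 uses the same word, terminated, with an end date. Lack of power does not make an already scheduled descriptive time point dispensable.

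**Conclusion.** The point holds in a limited form. As written, a group that receives no third vaccination loses the day-183 visit: one humoral sample per volunteer, 8 in an active group, nominally 119 days after dose 2, plus the safety bloods and adverse event interview. One or two of the four day-183 comparisons go with each active group stopped. The loss is most costly for a group stopped for a sufficient response, because no other sample could show whether that response lasts.

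The mismatch with section 8.2 is real as drafting but small in effect, and the 9-day and 159-day gaps should not be presented as a cost of stopping.

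This rests on two assumptions: that ending the group's study means no further study visits, which section 3 supports for non-responders and which is inferred for a sufficient response; and that doses and visits fall on their nominal days. It is a modest improvement worth making because it is cheap.

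**What to change.** Reconcile the synopsis (interim report), sections 3, 5.2.2 and 10.8, and section 8.2, so that withholding the third vaccination is distinct from ending study follow-up. Specifically:
- State that in a stopped group the section 8.2 surveillance continues, counted from dose 2.
- Keep the already scheduled day-183 (176-187) visit for stopped groups, with the 10 mL humoral sample, the safety bloods and the adverse event interview.
- Analyse the day-183 time point in all groups under section 10.6, including those that were stopped.
- Reconcile the 3-week end date in section 3 with the Flow Chart, which places the decision 6 to 7 weeks after dose 2.

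The cost is protocol wording and at most one already planned visit per volunteer in a stopped group. The rule for when dosing stops is left as it is and is not assessed here.
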